We plan to use optimal, sparse 1:k matching with refined covariate balance[148, 149] to ensure that the patients who are in each group (donors and controls) are as similar as possible based on age, sex, race/ethnicity, BMI, systolic and diastolic blood pressure, hypertension, smoking history, and family history of CKD. Briefly, this method allows one to exactly match on a small number of covariates (in this sense the method is sparse because it does not consider all possible matched pairs). The matching algorithm allows the near fine balance on discrete covariates between the intervention and control group (this means the distribution of the covariate is the same in the two groups but individuals may be matched to others with different levels of the covariate, i.e., frequency matching). An advantage of this approach is that it allows prioritization for balance on certain covariates over others. Finally, individuals are matched to minimize the overall difference between individuals using Mahalanobis distance or difference in propensity score (in this sense the match is optimal). The number of matched controls will depend on the number of potential controls with the available data. For each cohort of matched controls, we will assess the quality of matches by 1) computing the standardized difference of means for each covariate, as well as two-way interactions and squares and 2) for continuous covariates, examining quantile–quantile (QQ) plots, which compare the empirical distributions of each variable in the donor and control groups. Covariates for which there is an imbalance (e.g., standardized mean difference greater than 0.1) may be discretized and matched either exactly or to achieve near fine balance. Because matching is part of the design phase (as opposed to the analysis phase), we can repeat the matching several times until an acceptable balance is achieved without inflating type I error rates. If not enough controls with a matching characteristic (e.g., family history of CKD) are identified for matching to LDs, then the presence of the characteristics in both LDs and controls will be corrected for with multivariable adjustment for the analyses in predicting outcomes. Given that causal analysis is a rapidly developing field we will additionally consider state-of-the-art methodologies for determining optimal matches as new discoveries are made in this field.

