#### Statistical analyses details

Log-rank tests and Kaplan Meier curves will be used as preliminary assessments to compare the risk of all-cause mortality and cardiovascular mortality, CVD, ESKD, CKD (eGFR < 45; eGFR < 30 ml/min/1.73m^2^), proteinuria, DM, and hypertension after index date between LDs and healthy controls. Our study is powered based on these analyses. Cox proportional hazards models will also be used to test for an increased risk of adverse outcomes in living LDs versus controls while directly accounting for the variables used for matching (to account for any possible residual imbalance between the cohorts similar to how one may adjust for characteristics in a randomized controlled trial to account for residual imbalance and to improve efficiency). In analyses involving Mayo LDs and their associated controls we will account for donation center (Mayo vs. UMN) as a covariate in the model. If the proportional hazards assumption fails, an alternative method such as an accelerated failure time model will be considered. Indeed, the risk of mortality and ESKD may disproportionately increase with long-term follow-up on the 60-year scale of this study [123, 130, 131]. A similar approach will be used to test for increased risk of outcomes for LDs versus controls after development of DM, hypertension, proteinuria, de novo kidney disease, or pregnancies with gestational hypertension or preeclampsia, but additional measures (e.g. matching, adjustment) will be used to account for the time of disease onset.

In order to evaluate biases in the selection of controls and ascertain outcomes, we will compare the risk of non-kidney-related cancer between donors and controls using the previously described methods. As cancer risk is lower in donors than the general population, we expect a similar lower risk in controls [150]. If controls are well matched, we do not expect the risk of non-kidney related cancer to differ between donors and controls. If a difference in cancer risk is identified, it may indicate imbalance in our matching and it will be further investigated using methods described in Shi et al. [151].

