We will also evaluate if the effect of donation differs across baseline characteristics (i.e. evaluate if a characteristic modifies the effect of donation) by testing the significance of the interaction term between donation and the characteristic in the model. These models will also allow us to assess the attributable risk of donation in LDs with certain characteristics at donation. We will specifically assess if age, BMI, smoking, donation eGFR, and race/ethnicity modify the effect of donation on ESKD and mortality. As a sensitivity analysis, the analyses will be repeated using a subset of REP controls having at least 5 years of medical history preceding the index date.

Logistic regression models fit using generalized estimating equations will be used to test for differences in the odds of gestational hypertension and preeclampsia between LDs and controls for all pregnancies occurring after the index date, while accounting for women having potentially multiple pregnancies. Adjustment variables to be considered in the model include: race/ethnicity, age at pregnancy, gravidity, and previous occurrence of pregnancy complications. Secondary analyses using logistic regression models will test for differences in the odds of these complications in the first pregnancy after the index date, adjusting for having previous pregnancies, and second pregnancy after the index date, adjusting for the occurrence of pregnancy complications in the first post-index date pregnancy.

A linear mixed effects model will be used to test the difference in the trajectory of eGFR over time between living LDs and healthy controls. This model will initially have a linear effect for time with subject-specific random intercepts and slopes, but natural splines will be used to investigate nonlinear temporal trajectories.

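### The pregnancy models do not carry over the matching-variable adjustment used in the Cox models, so residual confounding by baseline blood pressure, BMI and smoking is possible among women with a post-index pregnancy

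*Protocol article*

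**What the plan says.** Three parts of the Statistical considerations section bear on this.

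- **Matching** (Primary control group and matching algorithms). The two groups are to be "as similar as possible based on age, sex, race/ethnicity, BMI, systolic and diastolic blood pressure, hypertension, smoking history, and family history of CKD". One layer of the match is near fine balance, under which "the distribution of the covariate is the same in the two groups but individuals may be matched to others with different levels of the covariate". Balance is assessed for each cohort of matched controls, using standardized differences for the covariates, their squares and two-way interactions, with 0.1 given as an example of imbalance.
- **Cox models** (Statistical analyses details). These compare donors with controls "while directly accounting for the variables used for matching". The stated reasons are residual imbalance and efficiency.
- **Pregnancy models** (same section). "Logistic regression models fit using generalized estimating equations will be used to test for differences in the odds of gestational hypertension and preeclampsia" between donors and controls "for all pregnancies occurring after the index date, while accounting for women having potentially multiple pregnancies". The covariate sentence reads: "Adjustment variables to be considered in the model include: race/ethnicity, age at pregnancy, gravidity, and previous occurrence of pregnancy complications". The secondary logistic models take the first post-index pregnancy, "adjusting for having previous pregnancies, and second pregnancy after the index date, adjusting for the occurrence of pregnancy complications in the first post-index date pregnancy".

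No baseline blood pressure, BMI, smoking or family history of CKD is named for any of the three pregnancy models.

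**The concern.** The protocol gives two covariate rules. The rule for hypertensive pregnancy outcomes is the one that does not name baseline blood pressure, although blood pressure at the index date is the pre-exposure level of what these outcomes measure. No reason is given for the difference.

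The match cannot be assumed to cover the gap. It is built and checked on all donors and their controls, men and women of all ages; 43.0% of UMN donors are men and mean age at donation is 39.02 years (Table 1). The pregnancy analysis keeps only women with a pregnancy after the index date. Marginal balance in a whole cohort does not pass automatically to a subset defined by a later event.

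Aim (e), on pregnancy outcomes, depends on these three models. The overall hypothesis is that any donor excess is small. A modest shift in the odds ratio from baseline differences would be comparable with the effect sought, and could mask or mimic it.

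**Working it through.** **1. Is the adjustment supplied elsewhere?** Two passages might supply it.

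- The Cox paragraph extends a similar approach to outcomes occurring after onset of diabetes, hypertension, proteinuria, kidney disease or a complicated pregnancy. There the pregnancy complication is the starting point, not the outcome.
- The matching section falls back on multivariable adjustment when too few controls have a matching characteristic. That trigger is scarcity of controls, not imbalance in a later subset.

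Neither fills the gap. In addition, sensitivity control group iii is not matched on clinical characteristics at all.

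**2. Inputs for size.** The plan states no number of pregnancies, event rate, effect size or power for these outcomes, so it has no figure to reproduce. Everything below is conditional on assumed values. Only the 0.1 imbalance threshold comes from the plan.

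**3. One omitted confounder.** For a rare outcome and a normally distributed confounder, the factor by which the donor odds ratio is biased is approximately

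bias factor = (OR per SD of confounder)^(standardized difference in the subset)

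| OR per SD (assumed) | 0 | 0.1 | 0.2 | 0.3 |
|---|---|---|---|---|
| 1.3 | 1.00 | 1.027 | 1.054 | 1.082 |
| 1.5 | 1.00 | 1.041 | 1.084 | 1.129 |
| 2.0 | 1.00 | 1.072 | 1.149 | 1.231 |

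With three independent confounders in the same direction, at OR 1.3 to 1.5 per SD each, the exponent triples: 1.08 to 1.13 at 0.1 and 1.27 to 1.44 at 0.3.

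**4. Can a subset be unbalanced when the whole cohort is balanced?** One standard normal covariate was simulated with 1,000,000 people per group, balanced overall, OR 1.5 per SD for the outcome and no donor effect. Log-odds slopes for later pregnancy were set by group.

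| Slope, controls / donors | Subset standardized difference | Unadjusted OR (true 1.00) |
|---|---|---|
| 0 / 0 | -0.003 | 0.999 |
| 0 / -0.2 | -0.164 | 0.947 |
| 0.1 / -0.2 | -0.244 | 0.901 |
| 0 / -0.4 | -0.316 | 0.859 |

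Equal selection gives no bias. Unequal selection gives bias even though the whole cohort is balanced.

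**5. Illustration with two confounders.** Assume 700 women per group with one pregnancy each, control event rate 9%, and OR per SD of 1.6 for systolic pressure and 1.4 for BMI (independent). The model was integrated numerically for a true conditional OR of 1.5. Power is two-sided 5%, by normal approximation.

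| Donor difference on both (SD) | Unadjusted OR | Power |
|---|---|---|
| 0 | 1.48 | 62% |
| -0.1 | 1.37 | 43% |
| -0.2 | 1.27 | 26% |
| +0.1 | 1.60 | 78% |

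The 1.48 at perfect balance reflects non-collapsibility of the odds ratio, not confounding. With a true OR of 1.00, a difference of +0.2 SD on both gives 1.17.

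**The case against.** The strongest reply is that the covariate list is open. It gives variables to be considered, and nothing forbids adding blood pressure or BMI. The article is condensed, and a final covariate list may sit in an analysis plan that is not shown. This stands as far as wording goes: the models do not name these variables, which is less than excluding them. It does not remove the point, because the same section states an adjustment rule for the Cox models and a different list here. Leaving the choice open also makes any later addition discretionary.

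The design also gives some protection. Sex is a matching variable. The two-way interaction checks would cover terms such as sex by BMI and age by BMI. Some covariates may be matched exactly, and individual distance is minimized. Control validation excludes blood pressure above 140/90 mm Hg, allows controlled hypertension only in controls over 50, and excludes BMI above 40, which narrows the range among women of childbearing age. Previous complications may carry part of the blood-pressure risk. All of this reduces the likely imbalance. None of it conditions on later pregnancy, so none of it assures balance in that subset.

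A reader might infer that the donor effect is confounded, or that the match fails in this subset. The documents do not support that. They contain no data showing that selection into pregnancy differs by group, and under equal selection the systematic bias is zero. Chance imbalance remains, but it is sampling variation already reflected in the confidence interval.

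The fallback adjustment for family history of CKD is not limited to Cox models, so that variable is partly handled already.

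**Conclusion.** The concern holds as a gap in the plan, not as a demonstrated bias. The covariates named for the three pregnancy models do not carry over the matching-variable adjustment of the Cox models, and the plan describes no balance check among women with a post-index pregnancy. Residual confounding of the donor odds ratio is therefore possible, in either direction.

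The size ranges from nothing, if selection into pregnancy is alike in both groups, to roughly 3 to 7% on the odds ratio for one confounder at a standardized difference of 0.1, and up to about 23% at 0.3. This rests on assumed confounder strengths of 1.3 to 2.0 per SD. Several confounders in one direction would add up; in opposite directions they would partly cancel. The two-confounder illustration rests further on an assumed sample size and event rate, and on both differences having the same sign, so it should not be read as a forecast.

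**What to change.** In the pregnancy paragraph of Statistical analyses details, add index-date systolic and diastolic blood pressure, BMI and smoking history to the GEE model, with family history of CKD where available. Do the same in the first- and second-pregnancy logistic models as event numbers allow. For each control group, report standardized differences on these variables among women with at least one post-index pregnancy.

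The cost is a sentence or two of plan wording. Blood pressure, BMI and smoking history must be ascertainable for entry to the primary control group. Among UMN donors, blood pressure is unknown in 1.9% and BMI in 1.5% (Table 1). The downsides are a few more parameters when events are few, and some missing data on family history, which the plan only undertakes to attempt. If baseline balance in the subset turns out good, little is lost and the report can show it.

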### Existing studies of attributable long-term risk of kidney donation

Several studies have sought to estimate the attributable risk of donor nephrectomy on mortality, ESKD, CVD, and other outcomes. Single-center and registry studies comparing LDs to the general population have not shown increased long-term CVD, ESKD, or mortality risk [14, 44–54]. Indeed, studies of longitudinal renal function in LDs have shown a small annual increase in GFR or estimated GFR (eGFR) for more than 15 years after donation [94–98]. A number of studies with average follow-up of less than 10 years compared LDs to matched healthy controls and found no difference in CVD and mortality [52–54, 58]. However, a 2014 Norwegian study with a median follow-up of 18 years found increased CVD and mortality in LDs compared to healthy controls; the authors attributed the difference in their findings compared to prior ones to longer follow-up [55]. A subsequent study based on the same population reported an increased risk of ischemic heart disease in LDs [99]. Two studies – the 2014 study from the Norwegian group, the other from the United States (US) - reported an increased risk of ESKD among LDs [55, 56]. Studies of postdonation pregnancies, compared to the general population, have generally not identified an increased risk of adverse fetal or neonatal outcomes. However, two studies comparing postdonation to predonation pregnancies reported an increased risk of hypertensive complications in the postdonation pregnancies, and one study reported an increased risk of hypertensive complications compared to healthy selected non-donors [100–102].

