### Aims and hypotheses

The MARKD study aims to determine long-term attributable LD risk by comparing well-matched controls with LDs. LDs will be compared with matched controls to determine: (a) whether LDs are at greater risk for the rare outcomes of mortality and ESKD; (b) whether LDs are at increased risk for CVD, cardiovascular mortality, and/or increased risk of intermediate measures of kidney disease (proteinuria, CKD [eGFR < 45 and eGFR < 30 ml/min/1.73m^2^ ]); (c) whether the trajectory of eGFR differs between LDs and controls; d) whether there are differences in the above outcomes for those developing de novo kidney disease and/or disease that might affect the kidneys (e.g., hypertension, DM, proteinuria); and e) whether there are differences in pregnancy outcomes (e.g., preeclampsia) between LDs and controls. The overall hypothesis is that LDs will have relatively small, slightly increased, but clinically insignificant, differences in the incidence of ESKD, mortality, intermediate endpoints, and pregnancy complications compared to well-matched control groups.

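### The second-pregnancy model adjusts for complications in the first pregnancy after donation, so it does not estimate the attributable effect of donation and tends to understate a real one

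*Protocol article*

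**What the plan says.** Aims and hypotheses sets the target: "The MARKD study aims to determine long-term attributable LD risk by comparing well-matched controls with LDs". One of the listed questions is "whether there are differences in pregnancy outcomes (e.g., preeclampsia) between LDs and controls".

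Statistical analyses details plans three donor-control comparisons of gestational hypertension and preeclampsia:

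1. **All post-index pregnancies.** A logistic GEE model "for all pregnancies occurring after the index date, while accounting for women having potentially multiple pregnancies". On covariates: "Adjustment variables to be considered in the model include: race/ethnicity, age at pregnancy, gravidity, and previous occurrence of pregnancy complications". The list is provisional, and no time limit is put on the complication history.
2. **First post-index pregnancy (secondary).** Logistic regression for the "first pregnancy after the index date, adjusting for having previous pregnancies".
3. **Second post-index pregnancy (secondary).** Logistic regression for the "second pregnancy after the index date, adjusting for the occurrence of pregnancy complications in the first post-index date pregnancy". Here the covariate is stated outright, not as a candidate.

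The Background gives grounds to expect an effect of donation: "two studies comparing postdonation to predonation pregnancies reported an increased risk of hypertensive complications in the postdonation pregnancies". It cites a further study that found the same against selected healthy non-donors.

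**The concern.** Attributable risk is a total effect: how much more often the complication occurs because the woman donated, by whatever route. The planned risk calculator (Dissemination section) has the same target. No direct-effect estimand is named for the pregnancy outcomes.

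In model 3 the covariate follows the exposure. Two things go wrong if donation raises the risk of a complication.

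- **Mediation.** If a complicated first pregnancy itself raises the risk in the second, part of the donation effect passes through the covariate, and adjustment removes that part.
- **Collider bias.** If complications recur only because some women are more susceptible, the first complication is a common effect of donation and susceptibility. Among women with the same first-pregnancy result, donors are then on average less susceptible than controls, which pulls the donor-control contrast towards 1.

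Both routes push towards a smaller difference, which is also the direction of the study's overall hypothesis of small, clinically unimportant differences. A reassuring second-pregnancy result could therefore be partly produced by the model.

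**Working it through.** The protocol gives no event rate, effect size, sample size or power for pregnancy outcomes, so there is no figure of its own to reproduce. Direction and size were checked by simulation. **All numerical inputs are assumptions.**

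**Which covariates can follow donation**

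| Model | Covariate | Can it arise after donation? |
|---|---|---|
| First post-index pregnancy | earlier pregnancies | No, all precede index |
| Second post-index pregnancy | complication in first post-index pregnancy | Always |
| All post-index pregnancies | previous complications | From the second post-index pregnancy on, if not limited to before index |
| All post-index pregnancies | gravidity | Same |

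**Simulation A.** 400,000 women per scenario, donors and controls 1:1, baseline logit -3.2, per-pregnancy odds ratio 1.5 to 2.0, woman-level SD 0.8 to 1.2 on the logit scale, direct recurrence log-odds ratio 0 to 1. The ratio of the donation log-odds ratio with the first-pregnancy complication in the model to that without it was 0.96, 0.89, 0.96, 0.88, 0.90, 0.85, 0.89 and 0.81 over eight scenarios: shrinkage of 4% to 19%. Example: odds ratio 1.89 becomes 1.68; ln 1.68 / ln 1.89 = 0.519 / 0.637 = 0.81.

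**Simulation B.** 250,000 women per scenario, 25% donors, baseline risk 6%, half with a pre-index pregnancy. A second post-index pregnancy occurs in 60%, or in a variant in 40% after a complicated first. The table shows the 60% case. Each arrow runs from adjustment for pre-index history only to adjustment including post-index complications. Shrinkage = 1 - ln(OR after) / ln(OR before).

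| Per-pregnancy OR | Susceptibility SD | Recurrence log-OR | Second pregnancy OR | Shrinkage of log-OR | All-pregnancy OR |
|---|---|---|---|---|---|
| 1.5 | 0 | 1.5 | 1.59 → 1.50 | 13% | 1.53 → 1.50 |
| 1.5 | 1.5 | 0 | 1.37 → 1.28 | 22% | 1.38 → 1.35 |
| 1.5 | 1.0 | 1.0 | 1.43 → 1.33 | 20% | 1.44 → 1.41 |
| 2.4 | 0 | 1.5 | 2.62 → 2.29 | 14% | 2.50 → 2.38 |
| 2.4 | 1.5 | 0 | 2.00 → 1.73 | 21% | 2.01 → 1.92 |
| 2.4 | 1.0 | 1.0 | 2.36 → 2.01 | 19% | 2.26 → 2.14 |

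The smallest second-pregnancy change came in the 40% variant: 1.60 → 1.54, a log-odds-ratio shrinkage of 1 - 0.432 / 0.470 = 8%. Over all scenarios with an effect and recurrence, the second-pregnancy odds ratio fell by 4% (1 - 1.54/1.60) to 15% (1 - 2.01/2.36). The all-pregnancy odds ratio fell by 1% (1 - 1.50/1.52) to 5% (1 - 2.14/2.26).

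Four readings follow.

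- Row 1 shows mediation alone. The total second-pregnancy effect is 1.59, and the planned model returns 1.50, the direct effect.
- Row 2 shows susceptibility alone. The first-pregnancy odds ratio in that scenario is also 1.37, so the right comparison for 1.28 is 1.37, not the woman-specific 1.5.
- With a true odds ratio of 1, or no recurrence, the two adjustments agreed apart from simulation noise.
- Replacing pre-index parity by gravidity at each pregnancy moved the all-pregnancy odds ratio by 0.01 or less.

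**The case against.** **First-pregnancy risk followed by second-pregnancy risk given the first is a standard transition decomposition.** This is fair, and the model is legitimate under that name. But the plan presents it as a test of donor-control differences, under an aim of attributable risk, without saying that the contrast is conditional.

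**Only one of the three models is clearly affected, and it is secondary.** This stands. A reader might infer that all the pregnancy models are biased, and the text does not support that. The first-pregnancy model contains nothing that follows donation. The GEE covariates, "race/ethnicity, age at pregnancy, gravidity, and previous occurrence of pregnancy complications", are candidates only, and their timing may be settled in a fuller plan. Complications before index are proper confounders, because pregnancy history is not among the matching variables.

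**Gravidity.** A reader might also treat gravidity as a consequence of donation. The protocol does not say that it is, and it made no visible difference in the simulation.

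**The importance of pregnancy.** It would be wrong to call pregnancy the only outcome with cited evidence of donor harm. The Background also cites cardiovascular disease, mortality and ESKD.

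**Dropping the covariate can introduce a bias of its own.** This is the strongest point. Women with a second post-index pregnancy are a selected group. Suppose 60% continue after an uncomplicated first pregnancy but, after a complicated one, 20% of donors against 45% of controls (baseline logit -3.2, SD 1.2, recurrence log-odds ratio 1). With a true odds ratio of 1.0, the second-pregnancy odds ratio without the covariate was about 0.90, against 1.00 as planned; for all pregnancies it was about 0.96 against 1.00. With a per-pregnancy odds ratio of 2.0 the figures were 1.63 and 1.72, both below the 1.89 seen without selection. These continuation rates are assumed and strongly unequal. They show that deleting the covariate from model 3 is not a sufficient repair, and that the first-pregnancy analysis, which needs no second pregnancy, should lead.

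**Conclusion.** The concern holds for the second-pregnancy model. As specified, it does not estimate the attributable effect of donation. If donation raises risk, complications recur, and continuation to a second pregnancy does not differ strongly between donors and controls, it tends to understate the effect, with a log-odds ratio roughly 4% to 22% smaller over the scenarios tried. The direction was the same in all of these; the size depends on assumed baseline risk, effect, susceptibility and recurrence, none of which the protocol supplies.

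For the all-pregnancy GEE the point is conditional and small: an odds ratio about 1% to 5% lower, and only if post-index complications are counted as previous ones. The material does not show that the plan would hide a large donor harm, nor that it would produce a spurious effect where none exists. What is affected is what a second-pregnancy result may be said to show, and to a small degree the main pregnancy estimate.

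**What to change.** Three changes to the pregnancy paragraph of Statistical analyses details:

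1. Name the first-post-index-pregnancy model as the leading estimate of the donation effect, adjusted for pregnancies and complications before index. The current text has only earlier pregnancies.
2. In the all-pregnancy GEE, limit complication history to before the index date, and keep the version with any previous complication as a sensitivity analysis.
3. Report the second-pregnancy model given the first as recurrence risk (a conditional effect), not as a test of the attributable effect of donation.

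The cost is a few sentences. Table 2 already lists number and year of pregnancies and their complications, and the plan already has to split pregnancies at the index date, so no new data are needed and no pregnancies are dropped.

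The downside is that the GEE limited to pre-index history can be slightly biased if complications reduce further pregnancies differently in donors and controls. Tabulating continuation to a second post-index pregnancy, by group and first-pregnancy complication, would show whether this matters.
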